**Objective**

- **To determine the safety and tolerability of multi-doses of Orameds oral insulin in people with type 1 diabetes**

Secondary Outcome Measures:

**To determine if oral insulin is likely to improve glycemic stability assessed by the reduction of the frequency and severity of hypoglycemic episodes in people with unstable type 1 diabetes**

**Diabetes** has emerged as a primary health threat of the 21st century. The condition formally termed *diabetes mellitus* is a hormone disorder signified by the cells’ inability to absorb glucose from the blood. This can occur either when there is not enough insulin in the blood, or when the body’s cells fail to respond normally to the insulin that is present. In either case, the negative results are manifold: First, the blood becomes flooded by an overabundance of sugar, sending glucose concentrations in the blood shooting up to dangerous levels. Second, without insulin, muscle and liver cells cannot absorb glucose from the blood, so these cells lack sufficient sugar and are therefore starved for energy. As a result, the body’s supply of fats and proteins must be consumed for “fuel” to keep normal physiologically processes going, simultaneously both depleting the body’s energy storages and disrupting normal metabolic regulation of fats and proteins.

Hypoglycemia is prevalent in diabetes. The DCCT reported a threefold increasein severe hypoglycemia and coma in intensively treated patientsas compared to conventionally treated patients. An intensively treatedindividual with type 1 diabetes can experience up to 10 episodesof symptomatic hypoglycemia per week and severe temporarilydisabling hypoglycemia at least once a year. An estimated2-4% of deaths of people with type 1 diabetes have been attributedto hypoglycemia. Hypoglycemia is less common and generally less severe intype 2 diabetes, but is not uncommon in clinicaltrials using insulin to achieve good metabolic control.

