Among insulin dependent diabetic subjects there is a subgroup of individuals who exhibit swings of extremes of hyperglycemia to hypoglycemia for no obvious reason. Such patients are defined as having the syndrome of “unstable” or brittle diabetes and they tendto defy all attempts at orthodox glycemic control and the conditiondisrupts the lives of themselves, their relatives and their healthcare teams, recurrentand long hospital admissions are the rule. The peak age-groupfor brittle “unstable” diabetes is 15-30, but it can occur in older patients as well as in younger individuals. Suggested causes included subcutaneous insulin degradation, impaired hyperemic responses to insulin injection, and enhanced insulin clearance. Presently, it is believed that "Pure" recurrent hypoglycemia is associated with loss of awareness of low glucose concentration. The syndrome of recurrent severe and asymptomatic hypoglycemia, associated with delayed adrenergic and autonomic counterregulatory responses, has been recognized in patients receiving intensified insulin treatment and may result from rather than be the initiating cause of recurrent hypoglycemia. The vicious circle that results, however, makes it particularly dangerous for these patients as it is reported to be a cause of mortality amongst them.

The normal counter regulatory responses to hypoglycemia is basically as follows; a decrease in plasma glucose normally triggers a cascade of reactions, mostly hormonal, that rapidly return the glucose concentration to baseline levels. Ultimately there is an increase in glucose production in the liver (and kidneys) and a decrease in peripheral glucose utilization. Both mechanisms act in opposition to the effects of insulin and, hence, result in the reversal of hypoglycemia.

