**Study Design**:

- The patient will be screened and an informed consent be obtained. A total of 8-12 type 1 diabetic patients with known uncontrolled type 1 diabetes will be recruited into this study at one investigational site. Patients will remain on their current medication with no changes to dose or regimen. Patients will undergo 5 days of run-in period whereby data from the CGM will be collected to assess the glycemic swings. The data will serve as a base-line for comparison. After the 5 day run-in period patients will be administered oral insulin for duration of 10 days. Oral insulin will be administered in one capsule given 45 min. before each meal. (The intervals of 5, and 10 days were chosen based on the life of the sensor- The average sensor lif3e is 5 days at which point it needs to be changed).
- Hypoglycemic episodes will be assed by clinical reporting and by Continuous glucose monitoring (CGMS). CGMS consists of a sterile disposable subcutaneous glucose-sensing device connected by a cable to a glucose monitor. The system allows downloading and reviewing of the data on a personal computer. The sensing device (needle) detects glucose levels in the subcutaneous interstitial fluid electrochemically (reaction with glucose oxydase) and registers it at frequent intervals, the data collected is stored and will be analyzed at the completion of the study.
- Hypoglycemia severity grading: Mild (grade 1) - Patient is aware of, responds to and self-treats the hypoglycemia Moderate (grade 2) -Patient cannot respond to hypoglycemia and requires help from someone else, but oral treatment is successful, Severe (grade 3) - Patient is semi-conscious or unconscious or in coma ± convulsions and may require parenteral therapy (glucagon or IV glucose)

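### Safety is the primary objective, but hypoglycaemia and CGM are not named safety evaluations, and no CGM review is scheduled while dosing can still be changed

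*Protocol*

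**What the plan says.** The Objective section sets the primary aim: "To determine the safety and tolerability of multi-doses of Orameds oral insulin in people with type 1 diabetes". Hypoglycaemia appears there only as a secondary outcome and only as a hoped-for benefit, "assessed by the reduction of the frequency and severity of hypoglycemic episodes in people with unstable type 1 diabetes".

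Under Study Design and Treatment Regimen, a 5-day run-in with CGM is followed by 10 days of one 8 mg capsule before each of three daily meals, again with CGM. Background treatment is fixed: "Patients will remain on their current medication with no changes to dose or regimen". Episodes are assessed by clinical reporting and by CGM, with three severity grades. The mildest grade reads "Patient is aware of, responds to and self-treats the hypoglycemia"; the other two require another person's help or impaired consciousness. On handling of the CGM data, the section says "The system allows downloading and reviewing of the data on a personal computer" and then "the data collected is stored and will be analyzed at the completion of the study". It gives no other time for looking at them.

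Safety Evaluations lists adverse events, concomitant medication, vital signs, chemistry and haematology, and physical examination. End of Study/Early Discontinuation lists vital signs, laboratory tests and physical examination. Neither section mentions hypoglycaemia, glucose or CGM. Early discontinuation is provided for, but no hypoglycaemia criterion for it is given.

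**The concern.** The trial adds insulin to an unchanged regimen in patients with uncontrolled type 1 diabetes, and its main question is whether that is safe. Hypoglycaemia is the obvious risk to examine. The trial records glucose continuously, yet the protocol places those data outside the named safety evaluations and plans no look at them until dosing is over.

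The data at issue are lows that nobody notices. The protocol's background, in discussing unstable diabetes, says that "recurrent hypoglycemia is associated with loss of awareness of low glucose concentration", and the secondary outcome is aimed at unstable patients. The eligibility criteria neither require nor exclude impaired awareness. If a patient has marked unnoticed lows early in treatment, the study physician has no scheduled occasion to see them and decide whether that patient should continue. At the end, such lows would not be a named finding under the primary objective.

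**Working it through.** There is no planned statistical figure to reproduce. The check compares the sections with each other and counts exposure.

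**Which procedure would catch which event**

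| Event | Clinical report or adverse event | Severity grade | Named safety evaluation | Scheduled CGM look during dosing |
|---|---|---|---|---|
| Noticed and self-treated | Yes | 1 | Through adverse events | None |
| Needs help, oral treatment works | Yes | 2 | Through adverse events | None |
| Impaired consciousness | Yes | 3 | Through adverse events | None |
| Unnoticed, resolves unaided | Unlikely | None fits | No | None |

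Only the last row is uncovered. Within the procedures described, CGM is the only instrument that would record it. Such a low can still count towards the secondary frequency outcome once the CGM data are analysed. Patients' routine glucose checks, which might catch some of these lows, are not described.

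**Inputs**
- Run-in 5 days, treatment 10 days, average sensor life 5 days (Study Design).
- Three capsules a day of 8 mg each (Treatment Regimen).

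**As written, per patient**
- CGM days before a planned look: 5 + 10 = 15.
- Doses before a planned look: 3 × 10 = 30 capsules, or 30 × 8 = 240 mg.
- Completion of the study may mean the patient's own last visit or the end of the trial. Either way it comes after that patient's last planned dose.

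**With reviews at the sensor changes already due**
- Sensors needed: 15 / 5 = 3, so changes fall at about study day 5 (end of run-in) and study day 10 (treatment day 5).
- Longest stretch with no scheduled review: 5 days, with looks at days 5, 10 and 15.
- Doses before the first on-treatment review: 3 × 5 = 15 capsules, or 15 × 8 = 120 mg.
- The last 5 treatment days would still wait for the end of the study.

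**How often it might matter.** The protocol gives no rate of marked unnoticed lows. For an assumed proportion p of patients with such lows in treatment days 1–5, the chance of enrolling at least one is 1 − (1 − p)^n:

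| p (assumed) | n = 8 | n = 12 |
|---|---|---|
| 5% | 33.7% | 46.0% |
| 10% | 57.0% | 71.8% |
| 20% | 83.2% | 93.1% |

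This is an illustration only. It does not measure how often a day-5 review would change management or prevent harm.

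**The case against.** The case on the other side has six parts, and much of it stands.

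- **Hypoglycaemia is monitored.** A reader might infer from the Safety Evaluations list that episodes go uncollected. They do not: Study Design provides clinical reporting, CGM and a grading scale, and adverse events are collected from consent to the end-of-study evaluations.
- **An increase would be visible.** A reader might also infer that the trial could miss a rise in hypoglycaemia altogether. The run-in is the stated baseline, and the secondary comparison would show an increase as readily as a decrease. What is missing is its status as a finding under the primary objective.
- **Early looks are not forbidden.** The sentence about analysis at completion may simply describe the formal analysis, and download is possible at any time. That is correct, but no look is planned either.
- **Patients who live alone are excluded** (listed after Sample Size). A low that progresses to needing help is therefore more likely to be seen and reported. This reduces the potential harm but does not reach lows that resolve unaided.
- **Little hypoglycaemia is expected.** The background argues that little oral insulin reaches the periphery and reports that the product has not caused hypoglycaemia. The trial exists to test safety, so this expectation cannot replace monitoring.
- **Acting on mid-treatment CGM could disturb the comparison.** In a single-arm study of 8–12 patients with background treatment held fixed, this is a real cost and has to be weighed. It argues for careful recording of any change. It does not argue for leaving the data unreviewed.

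How hypoglycaemia is summarised can be left to an SAP. Which evaluations count as safety, and when a physician looks at them during dosing, are matters of trial conduct that this protocol itself sets out.

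**Conclusion.** The concern holds in a narrow form and should be fixed. Unnoticed, self-resolving lows fit no severity grade, are not a named finding under the primary objective, and have no scheduled review while dosing can still be changed. Noticed episodes are covered.

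The size that the protocol supports is procedural. The longest stretch with no scheduled review would fall from 15 to 5 CGM days, and the first on-treatment review would come after about 15 doses instead of after all 30. This assumes that sensors are changed at about their stated average life and that the patient completes treatment. The 34%–93% range should not be read as an estimate of risk or benefit, because it rests wholly on an assumed 5%–20% rate.

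**What to change.** 1. **Safety Evaluations:** name hypoglycaemia as a safety outcome, both clinically reported and CGM-detected, including CGM lows that fit no severity grade. State that an increase per day from run-in to treatment counts under the primary objective. This uses data already collected and costs only wording; analysis details can stay in the SAP.
2. **Study Design:** download and review CGM at the two sensor changes already due, at the end of run-in and at about treatment day 5. Set in advance a glucose level and duration that refers the patient to the study physician for a decision on continuation. The run-in review gives each patient's own baseline for judging the day-5 data.

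The end-of-run-in review can use the contact already set for vital signs at that point, so only the day-5 review needs an added contact or download. The main downside is that any safety-driven insulin change departs from the fixed background regimen and affects the before-after comparison. Recording does not remove that effect, so the date and dose of each change must be recorded and reported with the results.

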**STUDY DURATION**:

**Screening Phase:** up to 14 days prior to first dose of study medication

Pre treatment phase: 5 days

**Treatment Phase:** 10 days.

**End of Study:** After completion of Period 2 or at early discontinuation

**SCREENING PHASE**:

Screening may take place up to 14 days prior to first dose of study drug administration. The following evaluations will be performed after the subject signs informed consent:

- Medical history
- Physical examination
- Medication history
- Vital signs (blood pressure, heart rate). Vital signs will be measured in the sitting position after at least 5 minutes of rest.

Clinical laboratory evaluations (chemistry, hematology)

**TREATMENT PHASE**

The Treatment Phase will consist of two periods:

1. Pretreatment phase in which the volunteers will have only his CGM for 5 days.

2. Treatment phase in which the volunteers will start medication before each meal (3 times/day) for 10 days including CGM.

**END OF STUDY/EARLY DISCONTINUATION:**

After completion of Period 2, subjects will complete the following end of study evaluations:

- Vital signs (blood pressure, heart rate) will be measured in the sitting position after at least 5 minutes of rest.
- Clinical laboratory evaluations (hematology, chemistry)
- Physical Exam

Subjects who are discontinued early from the study will complete the end of study evaluations at the time of early discontinuation.

**TREATMENT REGIMEN**:

The treatment regimen is as follows:

1. Period 1: no added medication. 5 days CGM. No change in current treatment.
2. Period 2: For 10 days one capsule of insulin before each meal (3 time/day). Each capsule contains: 8 mg insulin.

**SAFETY EVALUATIONS:**

- Adverse events will be collected throughout the study beginning from the time the subject signs the consent form until the end of study evaluations
- Concomitant medications/therapies will be recorded throughout the duration of study, beginning from the time the subject signs the informed consent.
- Vital signs (blood pressure, heart rate) will be measured in the sitting position after at least 5 minutes of rest at the following times:
- Screening
- At the end of period 1
- End of study
- Clinical laboratory evaluations (chemistry, hematology) will be performed at screening and at end of study or early discontinuation. .
- Physical examinations at screening and end of study or early discontinuation.

**SAMPLE SIZE:**

12-8 Type 1 subject – HbA1C: 7.5-10.

Inclusion Criteria:

- Type 1 diabetes mellitus based on clinical dependence on insulin and positive GAD measurements.
- Male or female aged 18-50 years inclusive
- Body weight between 50 - 100kg and body mass index between 18 and 30 kg/m2
- Diagnosed 6 or more months ago
- No other known medical problems that may affect the safety of the patient or the results of the study (as assessed by the study physician).

Exclusion Criteria:

- History or presence of clinical significant gastrointestinal pathology or symptoms, liver or kidney disease or any condition that might interfere with the absorption, distribution, metabolism or excretion of the drug.
- Positive pregnancy test or lactation
- Lack of family support (patient lives alone)
- Unwilling or unable to follow the study protocol
- Concurrent medical problems

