Different counter regulatory mechanisms are activated at different threshold levels of glucose concentration. The first defense against a falling plasma glucose concentration is a decrease in endogenous insulin secretion. This mechanism is critical in patients with residual endogenous insulin secretion. Of the other hormones, epinephrineand glucagonappear to be the most potent counter regulatory factors and are the primary fast-acting hormonesin the defense against acute hypoglycemia. These hormones are secreted promptly after plasma glucose levels fall, and both induce a rapid increase in endogenous glucose production. Glucagon acts toincrease endogenous glucose production and does so via increasesin hepatic glycogenolysis and gluconeogenesis, providing threecarbon glucose substrates (lactate, pyruvate, alanine, and glycerol).Epinephrine can also acutely increase endogenous glucose production.Epinephrine has effects similar to glucagon on hepatic glucoseproduction but can also stimulate net renal glucose production. Additionally,epinephrine has an important physiological function in reducing insulin-stimulatedglucose uptake. Other major counter regulatory hormones seem to be less critical in the initial phase of a hypoglycemic episode but are important in the later stage of glucose stabilization. Cortisoland growth hormoneboth help the liver to sustain glucose output in the face of hyperinsulinemia. In addition, these hormones reduce peripheral glucose use during recovery from hypoglycemia, an action shared by epinephrine.

An appropriate increase in endogenous glucose production (EGP)is critical for the recovery from **hypoglycemia. B**oth Glucagon and epinephrine act toincrease endogenous glucose production via increasesin hepatic glycogenolysis and gluconeogenesis, the two majorsources of glucose-6-phosphate destined for dephosphorylationand glucose release. Glycogenesis and glycogenolysis take placesimultaneously, with the preponderance favoring glycogenolysiswhen an increase in EGP is required, whereas gluconeogenesisis favored in the fasting, postabsorptive state. Recent studies suggest that glycogenbreakdown may be the primary mechanism responsible for the increasein EGP during the initial recovery from insulin-induced hypoglycemia,followed by an increase in gluconeogenesis.

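### The entry criteria do not select the unstable patients named in the secondary objective, so the hypoglycaemia result may not speak to them

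*Protocol*

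**What the plan says.** The protocol describes the study population in three ways.

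- **Secondary objective (Objective).** The aim is "reduction of the frequency and severity of hypoglycemic episodes in people with unstable type 1 diabetes". The background text that follows explains the term: "a subgroup of individuals who exhibit swings of extremes of hyperglycemia to hypoglycemia for no obvious reason".
- **Study Design.** "A total of 8-12 type 1 diabetic patients with known uncontrolled type 1 diabetes will be recruited". The term *uncontrolled* is not defined, and *unstable* is not used.
- **Sample Size and the inclusion list below it.** The disease criterion is "Type 1 diabetes mellitus based on clinical dependence on insulin and positive GAD measurements". The other criteria cover age, weight and BMI, at least 6 months since diagnosis, and no other relevant medical problem. HbA1c 7.5–10 appears in the sample-size line above the list.

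Study Design uses the 5-day run-in with continuous glucose monitoring (CGM) as the baseline for comparison. No eligibility threshold is attached to it. The primary objective, safety and tolerability, is stated for people with type 1 diabetes without restriction.

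**The concern.** A patient can meet every written criterion without ever having shown the swings that define the secondary objective's population. The only measure of control is HbA1c. It reflects average glucose, so it cannot separate steady hyperglycaemia from alternating highs and lows.

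The secondary outcome is a reduction in episodes from a 5-day baseline. A patient with no baseline episode cannot show a reduction in frequency; the count can only stay at zero or rise. With 8–12 patients, each such patient is a large part of the data. If several are enrolled, neither a favourable nor an unfavourable result answers the question for unstable diabetes. Mitigating instability is also the intent that the background gives for the study. Eligibility is fixed in the protocol, so an analysis plan could not repair this later.

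**Working it through.** **Comparison of the texts.** The objective requires instability, meaning swings that include hypoglycaemia. Study Design requires lack of control, undefined. The criteria require insulin-dependent, GAD-positive disease, with the HbA1c range. None of the listed criteria refers to episode counts, hypoglycaemia unawareness, glucose variability or a run-in CGM value. The mismatch follows from the wording alone and needs no calculation.

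**How many patients might have no baseline episode.** The 8–12 patients are stated without a rate, effect size, alpha or power, so there is no figure of the plan to reproduce. The inputs for a check of the consequence are:

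- run-in of 5 days (Study Design);
- n = 8 and n = 12 (Study Design, Sample Size);
- up to 10 symptomatic episodes per week, an upper figure for intensively treated patients (background under Objective);
- 0.5, 1 and 2 episodes per week, which are assumptions of this review.

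With Poisson counts at weekly rate r, the chance that a patient has no episode is P0 = exp(−r × 5/7), and the expected number of such patients is n × P0.

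| r per week | Source | r × 5/7 | P0 | of 8 | of 12 |
|---|---|---|---|---|---|
| 0.5 | assumed | 0.357 | 70% | 5.6 | 8.4 |
| 1 | assumed | 0.714 | 49% | 3.9 | 5.9 |
| 2 | assumed | 1.429 | 24% | 1.9 | 2.9 |
| 10 | protocol, upper figure | 7.143 | 0.08% | 0.01 | 0.01 |

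The binomial chance that at least half the group has no run-in episode, for n = 8 and n = 12, is 94% and 96% at 0.5 per week, 61% and 58% at 1 per week, and 10% and 4.5% at 2 per week.

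**Sensitivity to the Poisson assumption.** If rates differ between patients, more of them have none. For a negative binomial with mean m = r × 5/7 and an assumed k = 0.5, P0 = (k/(k+m))^k. This gives 76%, 64%, 51% and 26% at 0.5, 1, 2 and 10 per week. The very small Poisson figure at 10 per week therefore holds only if all patients share that rate.

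**The case against.** The strongest reply is that the study is first a small safety study. Its primary objective covers type 1 diabetes in general, and the criteria fit that. This stands, and it limits the point to the secondary outcome.

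Second, the rates of 0.5 to 2 per week come from no document. The only symptomatic rate in the protocol leaves almost nobody without a run-in episode under the Poisson model. Episodes are also assessed by CGM as well as by clinical report, so asymptomatic lows could raise the counts. This stands too: the consequence is possible, not shown.

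Third, the HbA1c range sits directly above the inclusion list, and Study Design calls for known uncontrolled patients. In practice, then, not every GAD-positive adult would be enrolled. That is fair, but poor control on average is still not instability.

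A reader might go further in two ways that the documents do not support.

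- One might infer that an HbA1c floor selects away from hypoglycaemia, because the background reports a threefold increase in severe hypoglycaemia under intensive treatment. That comparison is between treatment strategies, without HbA1c values. The background also says that poorly controlled patients build up poor liver glycogen stores and that, for many patients, this raises vulnerability to hypoglycaemia. The direction is not established.
- One might infer that the 6-month rule admits patients with residual insulin secretion. Of the fall in endogenous secretion as a defence, the background says "This mechanism is critical in patients with residual endogenous insulin secretion", but nothing in the protocol links 6 months since diagnosis to such secretion.

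**Conclusion.** The mismatch is certain from the text: the secondary objective is about unstable diabetes, and no entry criterion identifies it. What follows for the data is uncertain. Under Poisson counts, the expected number with no run-in episode is about 6, 4 and 2 of 8 patients, or 8, 6 and 3 of 12, at the assumed 0.5, 1 and 2 episodes per week. It is practically none at the protocol's upper figure of 10 per week. Variation between patients would raise these numbers, and CGM-detected episodes would lower them.

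It would be too strong to say that the trial will fill with patients who have nothing to reduce, or that the trial as a whole fails. The protocol gives no rate for its own population, and the safety objective is untouched. The point is a should-fix, confined to the secondary outcome and the conclusion drawn from it.

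**What to change.** Before enrolment:

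1. Use one population term in Objective, Study Design and the criteria, and define it.
2. Move the HbA1c range into the inclusion list.
3. Then choose one of two routes.
   - **Add an operational criterion** for instability or hypoglycaemia history, assessed from records before the run-in. The sponsor should justify the threshold against the length of the run-in: even at a true rate of 2 episodes per week, 24% of patients would have none in 5 days under the Poisson assumption. The run-in CGM should not be used for selection. Choosing patients for a bad baseline builds regression to the mean into a before-after comparison that has no control group, and this would look like benefit.
   - **Reword the secondary objective** to type 1 diabetes in general and limit the conclusion accordingly.

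Both routes are wording changes to the protocol. The first may slow recruitment at the single site, since the protocol itself calls unstable patients a subgroup. The second costs nothing in recruitment but gives up the claim about unstable diabetes.
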